**Study design**

This prospective, evaluator-blinded, randomized, controlled parallel-arm trial will be conducted at Sun Yat-sen Memorial Hospital, Sun Yat-sen University, China. The study protocol is approved by the Medical Ethics Committee of Sun Yat-sen Memorial Hospital of Sun Yat-sen University (Approval number: 201806). All procedures will be performed in accordance with the declaration of Helsinki. Written informed consent was obtained from every patient before randomization.

**Patients**

Patients with primary liver cancer who is scheduled for open hepatectomy with ERAS programs (**Table 1**) will be evaluated for eligibility. Inclusion criteria are as follows: age between 18 and 65 years; body mass index of 18.5-28 kg/m^2^; number of tumor less than 3; tumor’s maximum diameter or sum of diameters smaller than 10 cm; class A or B of Child-Pugh liver function; tumor’s clinical stage as I or II; the remaining liver volume/standard liver volume ratio of >40%; no difficulty of intubation or inserting an LMA; American Society of Anesthesiologist physical status classification between I and III. Exclusion criteria are as follows: presence of comorbidities such as diabetes, pathological cardiopulmonary disease and renal insufficiency; a New York Heart Association class of heart function of III or greater; intrahepatic vascular invasion or extrahepatic metastasis of tumor seen by computerized tomography (CT) or magnetic resonance imaging (MRI); having received chemotherapy or radiotherapy before surgery; having undergone abdominal surgery; infection of the site of TAP block; allergy to any study medication; a history of alcohol or drug abuse; difficulty of communication with family or hospital staff. After randomization, patients who experience a failure of TAP block or LMA ventilation, suffer systemic poisoning from local anesthetic, are found to have extensive metastasis of tumor after laparotomy, lose blood over 1000 ml during surgery, undergo a long operating time of over 6 hours (hr), need to be transferred into intensive care unit (ICU) after surgery, or refuse to go on participating in this trial will br excluded from the analysis.

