**Figure 1 Flow diagram for this trial**

**Interventions**

Patients in both groups will receive the same ERAS program except for the different interventions. For the control group, patients will be treated with endotracheal intubation for ventilation after anesthesia induction, a preoperative TAP block with 40 ml normal saline as control and local wound infiltration with 40 ml solution of ropivacaine 3 mg/kg plus dexamethasone 0.1 mg/kg at the conclusion of surgery. On the contrary, patients in the TAP+LMA group will have an LMA inserted for ventilation after induction, have a TAP block with 40ml solution of ropivacaine 3 mg/kg plus dexamethasone 0.1 mg/kg, and receive local wound infiltration with 40 ml normal saline at the conclusion of surgery. Guided by ultrasound, a subcostal TAP block will be performed bilaterally at the parasternal line and at the anterior axillary line, with 10ml solution injected in each site (**Figure 2**).

[figure not shown]

[figure not shown]

[figure not shown]

[figure not shown]

[figure not shown]

[figure not shown]

[figure not shown]

[figure not shown]

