**Study end-points**

The primary end-point of the study is postoperative time of readiness for hospital discharge. The discharge criteria include: pain score less than 4, solid diet without infusion, normal bowel movement, well-healed wound, normal organ function, normal count of white blood cell (WBC), no fever, life independence.

The secondary end-points are postoperative analgesic requirement within 48 hr, time to first flatus and overall medical cost. Blood glucose and lactate will be tested before anesthesia (t0), at surgical exploration (t1), at the conclusion of surgery (t2) and at departure from the post-anesthesia care unit (PACU) (t3). Dosages of anesthetics and vasoactive drugs, surgery duration, anesthesia duration, hepatectomy duration, duration of hepatic blood flow occlusion, bleeding volume, infusion volume and urine volume are recorded.

The postoperative pain intensity of the surgical site is assessed with the numerical rating scale (NRS), in which 0 represented no pain and 10 represented the most severe pain. Postoperative variables such as time to removing ETT or LMA, duration of PACU stay, time to first mobilization off the bed, incidence of nausea/vomiting within 48 hr and complications are also recorded and compared. The 40-item quality of recovery (QoR-40) survey is performed before surgery, at 1 and 3 days after surgery, and on the day of discharge, referred to other studies^[12, 13]^ and described as **the following figure**.

| **QoR-40 Questionnaire** | | | | | | | | |
| --- | --- | --- | --- | --- | --- | --- | --- | --- |
| Date:____/____/____ | Preoperative:_______ | | | Postoperative:______ | | | Study #:______ | |
| **PART A** | | | | | | | | |
| ***How have you been feeling in the last 24 hours?*** | | | | | | | | |
| (1 to 5, where: 1 = none of the time [poor], 2 = sometimes, 3 = often, 4 = most of the time, 5 = all of the time [excellent]) | | | | | | | | |
|  | | none of  the time | sometimes | | often | most of  the time | | all of the time |
| 1.Able to breathe easy | | 1 | 2 | | 3 | 4 | | 5 |
| 2.Being able to enjoy food | | 1 | 2 | | 3 | 4 | | 5 |
| 3.Have a good sleep | | 1 | 2 | | 3 | 4 | | 5 |
| 4.Feeling rested | | 1 | 2 | | 3 | 4 | | 5 |
| 5.Feeling comfortable | | 1 | 2 | | 3 | 4 | | 5 |
| 6.Having a general feeling  of well-being | | 1 | 2 | | 3 | 4 | | 5 |
| 7.Feeling in control | | 1 | 2 | | 3 | 4 | | 5 |
| 8.Able to write | | 1 | 2 | | 3 | 4 | | 5 |
| 9.Have normal speech | | 1 | 2 | | 3 | 4 | | 5 |

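### Randomised patients are excluded from the analysis for events after allocation, and one of these events, LMA failure, can occur only in the TAP+LMA arm, so the primary comparison can be biased

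*Protocol*

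**What the plan says.** The last sentence of the Patients section of the protocol sets out exclusions that apply once a patient has been randomised. It opens "After randomization, patients who experience a failure of TAP block or LMA ventilation, suffer systemic poisoning from local anesthetic". It then covers extensive metastasis discovered at laparotomy, patients who "lose blood over 1000 ml during surgery, undergo a long operating time of over 6 hours (hr", postoperative ICU transfer and refusal to continue. It closes "refuse to go on participating in this trial will br excluded from the analysis". The sentence is not limited to one analysis or one patient set, and the protocol names no other set.

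Under Interventions, for the control group "patients will be treated with endotracheal intubation for ventilation after anesthesia induction", whereas "patients in the TAP+LMA group will have an LMA inserted for ventilation after induction". Controls receive "a preoperative TAP block with 40 ml normal saline as control and local wound infiltration with 40 ml solution of ropivacaine 3 mg/kg". Both arms therefore have a block procedure and both receive ropivacaine, but only one arm has an LMA. Under Randomization and blinding, one anesthesiologist, who is aware of the assignment, performs every block and places every airway device.

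Under Study end-points, the primary end-point is time to readiness for discharge, overall medical cost is a secondary end-point, and "complications are also recorded and compared".

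**The concern.** Randomisation makes the arms comparable as they were allocated. Removing patients for something that happens afterwards keeps that comparability only if the event is unrelated to the allocation. LMA failure is tied to it entirely: it cannot happen to a control patient, and failed intubation is not on the list. TAP-block failure may also be recognised unequally. Failure is not defined, a saline block has no sensory effect whose absence could be noticed, and the person placing the block knows the arm.

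ICU transfer, blood loss and operating time also arise after allocation and may be influenced by it. ICU transfer bears directly on the primary end-point, because the discharge criteria include normal organ function and independence. It bears on cost as well.

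At stake is what the trial estimates. It would describe patients in whom the technique worked and surgery went smoothly, but the result would be read as the effect of choosing TAP+LMA. Some of the events used for removal are also results that the complication and cost comparisons ought to show.

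**Working it through.** **The plan's own figure.** Inputs from Statistical analysis and sample size: 9 (SD 2.5) versus 7.5 (SD 2.0) days, two-sided 0.05, 85% power. The common SD is √((2.5² + 2.0²)/2) = √5.125 = 2.264. The two-sample t-test has 84.2% power at 41 per group and 85.1% at 42, so the stated 42 per group is reproduced. With 48 per group and the full 1.5 days, power is 89.5%.

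**Bias from one-sided removal.** The protocol gives neither a failure rate nor the outcome of failures. Both are assumed here. Let a share f of patients in each arm be difficult cases who need e extra days, let there be no true treatment effect, and let only the TAP+LMA cases be removed. With m the mean of the other patients:

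- control mean = m + f × e
- TAP+LMA mean after removal = m
- bias = f × e in favour of TAP+LMA

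Type I error comes from simulation with 48 per arm, SD 2.5 within each subgroup and a pooled t-test at two-sided 0.05. The ranges are the spread over repeated simulations.

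| f | e (days) | bias (days) | share of 1.5 days | type I error |
|---|---|---|---|---|
| 2% | 4 | 0.02 × 4 = 0.08 | 5% | 5.2 to 5.4% |
| 5% | 2 | 0.05 × 2 = 0.10 | 7% | 5.2 to 5.7% |
| 10% | 4 | 0.10 × 4 = 0.40 | 27% | 10.1 to 10.5% |
| 15% | 4 | 0.15 × 4 = 0.60 | 40% | 16.4 to 17.4% |

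In an alternative model, only TAP+LMA patients can be failures and the arms have equal means as randomised. The bias is then the same and type I error is 5.6% (5%, 2 days), 11.7% (10%, 4 days) and 19.7% (15%, 4 days). If the same share is removed from both arms, there is no bias and type I error is about 5%.

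**Power when everyone is kept.** Suppose the planned 1.5 days applies only to patients without failure. The effect as randomised is then 1.5 − f × e, and the TAP+LMA variance rises to 2.0² + f(1 − f)e². With 48 per arm:

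- 5%, 2 days: effect 1.4, variance 4 + 0.19 = 4.19, common SD √((6.25 + 4.19)/2) = 2.28, power about 84%.
- 10%, 3 days: effect 1.2, variance 4 + 0.81 = 4.81, common SD 2.35, power about 69 to 70%.
- 10%, 4 days: effect 1.1, variance 4 + 1.44 = 5.44, common SD 2.42, power about 60 to 61%.

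**The case against.** Four points can be made for the plan, and each limits the finding.

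- **Direction.** A reader might infer that the comparison is biased towards TAP+LMA. The protocol does not show this. A patient whose LMA fails could go on to recover like any control patient, and then removal would do little. The direction follows only if failures recover later, which is plausible but not stated.
- **One-sidedness.** A reader might treat the whole list as striking one arm. Only LMA failure certainly does. Blocks are placed under ultrasound in both arms, so a technical failure could be seen with saline too. Ropivacaine toxicity, bleeding, long surgery and ICU transfer can occur in either arm, and the direction of their effect is open. Metastasis found at laparotomy is disease that was present before allocation, so excluding it is defensible if the judgement is blind to arm.
- **Size.** Eligibility already requires that no difficulty with intubation or LMA insertion is expected, which plausibly keeps LMA failure rare. At 2% failures the bias is under 0.1 day and type I error hardly moves.
- **Safety.** A reader might conclude that safety events vanish. Study end-points says that complications are recorded, and an SAP not shown here could define a safety set. What stands is narrower: as worded, the rule removes these patients from the complication and cost comparisons too.

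None of this rescues the rule. The exclusion is unrestricted, it is written in the protocol and not left to the SAP, and one of its criteria applies to one arm only.

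**Conclusion.** The point stands: the protocol fixes an analysis population that depends on events after randomisation, and at least one of them is specific to the experimental arm. This can bias the primary comparison. It favours TAP+LMA if failures recover later than other patients.

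The size cannot be taken from the protocol. Over the assumed range it runs from negligible (0.08 day, type I error close to 5%) to material (0.6 day, 40% of the planned effect, type I error about 17%). The upper figures need one-sided removal of 10 to 15% of an arm and 4 extra days. They illustrate what could happen and do not forecast it. The 15% drop-out allowance is no support for such a failure rate, since the protocol does not tie it to TAP or LMA failure.

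The defect governs the primary analysis. It should be corrected before data are analysed, because outcomes not followed after an exclusion may be unrecoverable.

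**What to change.** **Change to the protocol**

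- Define the primary analysis as all randomised patients in their assigned arm. Continue to record time to readiness, cost and complications after TAP or LMA failure, toxicity, large blood loss, long surgery or ICU transfer.
- Keep the present exclusion list only for a labelled per-protocol sensitivity analysis.
- Exclusion for metastasis found at laparotomy may stay if it is judged without knowledge of the arm and applied equally to both.
- For patients who withdraw consent, use data up to withdrawal and report the number by arm.
- Report LMA failure, TAP failure, local anaesthetic toxicity and ICU transfer by arm in all treated patients.

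**Cost.** The change needs revised wording and continued recording on patients who are already in hospital. It alters no treatment. The drawback is that the estimated effect, and with it the power, may be smaller once failures count. The 89.5% at 48 per arm holds only if the full 1.5 days applies to everyone randomised. The sponsor should therefore state which population the 1.5 days describes and check the sample size against it. It should not be assumed that keeping more patients makes up the loss.

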**Table 1 The ERAS program adopted in this trial**

| **Preoperative procedures** |
| --- |
| **·**Preoperative assessment, education and psychological counseling by talk, text and caption |
| **·**Preparation before admission: cessation of smoking and alcohol for 14 days, quick walk for 30 minutes daily, oral enteral nutritional powder if plasma albumin ≤30g/L, infuse red blood cell if Hb <70g/L |
| **·**No preoperative use of sedatives or anticholinergic drugs |
| **·**No bowel preparation, fasting for 6hr, and oral 10% glucose 500ml 2 hr before surgery |
| **·**No routine placement of gastric tube; if necessary, remove it as soon as possible |
| **·**Insert the urinary tube under lidocaine gel blockade and remove it within 48 hr |
| **·**Antibiotic prophylaxis 30min before surgery |
| **·**Use heparin to prevent deep vein thrombosis for high risk patients and monitor coagulation |
| **Intraoperative procedures** |
| **·**Continuously monitor body temperature and maintain its stability by warmed blanket, warmed infusion and preheated peritoneal irrigation |
| **·**Infuse crystal liquid mainly and restrict the volume (CVP ≤10 mmHg); rapidly infuse 200~300ml colloidal fluid if severe hypotension occurs during the implementation of controlled-low CVP |
| **·**No routine placement of peritoneal drainage tube; if necessary, remove it within 48 hours |
| **·**Anesthesia method: ETI general anesthesia for the control group, LMA general anesthesia combined with a subcostal TAP block for the TAP+LMA group |
| **·**Use of short-acting anesthetics (i.e. remifentanil, sufentanil, propofol and sevoflurane) |
| **·**Monitor anesthetic depth and maintain its stability |
| **·**Intravenous tropisetron 10mg for preventing postoperative nausea and vomiting |
| **Postoperative procedures** |
| **·**Multimodal postoperative analgesia: a. regional block (local wound infiltration for the control group and a subcostal TAP block for the TAP+LMA group); b. patient-controlled intravenous analgesia (PCIA) with sufentanil; c. intravenous parecoxib 40mg twice daily for 3 days; d. oral analgesic |
| **·**Assess pain intensity with numerical rating scale (NRS) and inject additional analgesic when NRS score≥5 |
| **·**Intravenouslydrip dexamethasone 5mg daily for 3 days to alleviate inflammation |
| **·**Treatment of postoperative nausea and vomiting |
| **·**Remove drainage tube and urinary tube as soon as possible |
| **·**Early oral intake: a little water on the day of surgery; liquid diet on 1^st^ postoperative day; semi-liquid  diet on 2^nd^ postoperative day; normal diet from 3^rd^ postoperative day on |
| **·**Early mobilization: exercise in bed on the day of surgery; walk in the ward at least twice on 1^st^ postoperative day; walk at least 4 times on 2^nd^ postoperative day; continuously walk from 3^rd^ postoperative day on |
| **·**Use low molecular weight heparin to prevent deep vein thrombosis |

**Randomization and blinding**

This study is an observer-blinded, randomized control trial. Randomization, stratified by surgeons, will be performed by independent personnel ([name]), through two random digit tables generated by computer software. The random digit and the information of group allocation for every enrolled patient is sealed with an opaque envelope. Two anesthesiologists ([name], [name]) will perform all the intraoperative assessments, and two other anesthesiologists ([name], [name]) will perform all the postoperative assessments; two surgeons ([name], [name]) will assess if the patients achieve the standard of hospital discharge, and two independent persons ([name], [name]) will perform the statistical analysis of the data. All these investigators are blinded to the group allocation. All procedures of TAP blockades and intubation or insertion of LMAs will be performed by the same anesthesiologist ([name]), who knows the group allocation. The flow diagram for this trial is summarized in **Figure 1**.

Identify patients with primary liver cancer

scheduled for open hepatectomy with ERAS programs

Review pre-operative assessment to determine eligibility

Obtaine informed consent

Perform randomization

(n=48)

Experimental group (TAP+LMA group):

a subcostal TAP block combined with LMA anesthesia

Control group:

general anesthesia with endotracheal intubation

Study end-points:

postoperative time of readiness for discharge; postoperative pain intensity;

time to first flatus; quality of recovery; complications; overall medical cost

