**Statistical analysis and sample size**

Statistical analyses will be performed with SPSS software version 19.0 (IBM Corporation, Armonk, NY, USA). Continuous variables are expressed as mean ± standard deviation and tested if they are normally distributed. Variables with normal distribution are compared between groups using a 2-sample Student’s *t*-test. Data without normal distribution are analyzed using non-parametric test. Blood glucose, lactate, the NRS pain score and the QoR-40 score will be compared between groups using repeated-measures analysis of variance (ANOVA). Categorical data is expressed as ratio or frequency and analyzed using Chi-square test or Fisher’s exact test. Two-tailed *P*<0.05 indicates statistical significance.

Based on our preliminary experiment consisting of 24 patients, the sample size for this trial is calculated using SAS software version 9.4 (SAS Institute Inc., Iowa City, IA, USA). The postoperative time of readiness for hospital discharge in the control group was (9 ± 2.5) days, while that of the TAP+LMA group was (7.5 ± 2.0) days. Accordingly, 42 patients are required per group to achieve 85% statistical power (1-β) at a significance level (α) of 0.05. To account for a 15% drop-out rate, we will enrolled 48 patients per group finally.

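### Randomisation is stratified by surgeon but none of the fixed analyses includes surgeon, so precision is forgone if surgeons differ in outcome

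*Protocol*

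**What the plan says.** Under Randomization and blinding, the Protocol says "Randomization, stratified by surgeons, will be performed by independent personnel", "through two random digit tables generated by computer software". It gives no number of operating surgeons, no block size and no rule that keeps the arms balanced within a surgeon.

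Under Study end-points: "The primary end-point of the study is postoperative time of readiness for hospital discharge".

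Under Statistical analysis and sample size, a test is named for each type of data. "Variables with normal distribution are compared between groups using a 2-sample" Student t-test. "Data without normal distribution are analyzed using non-parametric test". Blood glucose, lactate, NRS pain and QoR-40 go to repeated-measures ANOVA. "Categorical data is expressed as ratio or frequency and analyzed using Chi-square test or Fisher’s exact test". Surgeon appears in none of these, nor in the sample size, which rests on 9 ± 2.5 against 7.5 ± 2.0 days with 42 per group for 85% power.

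**The concern.** Stratifying by surgeon makes sense if surgeons may differ in outcome. Where they do, an analysis that ignores surgeon leaves the between-surgeon variation in the error term, while one that includes surgeon removes it. The design and the analysis therefore do not match.

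Two things are at stake. The first is power, in a trial planned on only 42 evaluable patients per arm. The second is whether the reported standard error is right. If the arms are balanced within surgeon, the treatment difference is free of surgeon variation, but the unadjusted test still charges for it. Confidence intervals are then too wide and the true type I error is below 5%.

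**Working it through.** **Inputs from the Protocol.** Difference 9 − 7.5 = 1.5 days; SDs 2.5 and 2.0; two-sided α = 0.05; power 85%; 42 per group.

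**Assumptions.** Two strata of equal size, since two random digit tables are mentioned but surgeons are not counted. The planning SDs are total SDs, because they are given for whole groups. The share of variance due to surgeon, s, is varied from 0 to 30%.

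**Reproducing the planned size.** Pooled SD = √((2.5² + 2.0²)/2) = √5.125 = 2.264 days. The normal approximation gives n = 2 × (1.960 + 1.036)² × 5.125 / 1.5² = 40.9, so 41 per group. The exact noncentral t gives 84.2% power at 41 and 85.1% at 42. The stated 42 is therefore the size for an unstratified two-group comparison.

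**Adding surgeon.** The error SD becomes 2.264 × √(1 − s), with 84 − 3 = 81 degrees of freedom. The standard error of the difference is 2.264 × √(2/42) × √(1 − s) = 0.494 × √(1 − s). With two equal strata, a share s corresponds to a gap between surgeons of 2 × √s × 2.264 days.

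| Share s | Surgeon gap (days) | Adjusted SE (days) | Adjusted power at 42 per arm | n per arm for 85%, normal approximation |
|---|---|---|---|---|
| 0% | 0 | 0.494 | 85.1% | 41 |
| 5% | 1.0 | 0.482 | 86.8% | 39 |
| 10% | 1.4 | 0.469 | 88.5% | 37 |
| 20% | 2.0 | 0.442 | 91.8% | 33 |
| 30% | 2.5 | 0.413 | 94.8% | 29 |

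**The unadjusted t-test, arms exactly balanced within surgeon** (simulation, 40,000 trials per setting, total SD held at 2.264). The SE ratio is the mean SE reported by the unadjusted test divided by the mean adjusted SE.

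| Share s | SE ratio | Type I error, unadjusted | Power, unadjusted | Power, adjusted |
|---|---|---|---|---|
| 0% | 0.492/0.492 = 1.00 | 5.0% | 85.1% | 85.1% |
| 5% | 0.493/0.480 = 1.03 | 4.4% | 86.0% | 87.1% |
| 10% | 0.493/0.467 = 1.06 | 3.8% | 86.3% | 88.4% |
| 20% | 0.494/0.441 = 1.12 | 2.7% | 87.3% | 91.7% |
| 30% | 0.494/0.412 = 1.20 | 1.9% | 89.1% | 94.7% |

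The adjusted test keeps its type I error near 5% throughout.

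**The unadjusted t-test, unrestricted allocation** (simulation, 20,000 trials per setting, 84 patients). At shares of 10%, 20% and 30%, unadjusted type I error is 5.2%, 5.0% and 5.2%. Power is 85.1%, 84.5% and 84.5% unadjusted, against 88.2%, 91.1% and 94.1% adjusted. The unadjusted standard error is then valid for its own estimate, but larger than the adjusted one.

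**The case against.** The strongest reply is that nothing in the plan is invalid. Ignoring surgeon does not create false positives, and the planned power is met without adjustment. All patients follow one ERAS programme and one set of discharge criteria, applied by the same pair of blinded assessors, so surgeons may differ little. A gap of 2 days would exceed the 1.5-day treatment effect. At shares of 5% to 10% the gain is only about 1 to 2 points with balanced arms. An unseen SAP might also add surgeon. All of this stands as a limit on the size of the point. It does not remove the mismatch, because the Protocol itself names the unadjusted tests.

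Three stronger readings are tempting, and the Protocol does not support them.

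- A reader might infer that the trial is underpowered. Adding a surgeon gap of 2 or 3 days on top of an SD of 2.26 gives unadjusted power of about 80% or 74%. That treats the whole-group SDs as within-surgeon SDs and raises the total SD to √(5.125 + 1²) = 2.47 or √(5.125 + 1.5²) = 2.72, a noisier trial than the one planned.
- A reader might infer that the standard errors are certainly too wide. That needs balance within surgeon, and no block scheme is stated. The exclusions after randomisation listed under Patients could also disturb such balance.
- A reader might infer that there are two operating surgeons because two surgeons are mentioned under Randomization and blinding. Those two judge discharge readiness and are not described as the strata.

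**Conclusion.** The point holds as lost efficiency, not as an error that threatens validity. The trial randomises by surgeon and fixes analyses that ignore surgeon. With two equal strata, 42 per arm and the planning SDs read as total SDs, unadjusted power stays at roughly 85% or above. Surgeon-adjusted power would be about 87%, 88%, 92% and 95% at surgeon shares of 5%, 10%, 20% and 30%. These shares are assumed; the Protocol offers no figure.

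The further statement that the unadjusted standard error is about 6%, 12% and 20% too large at shares of 10%, 20% and 30%, with type I error of roughly 4%, 2.5% and 2%, applies only if the arms are balanced within surgeon. Under unrestricted allocation type I error stays near 5%, and the power is still forgone. The mismatch reaches the primary end-point directly, and the repeated-measures and categorical analyses in the same way.

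**What to change.** In Statistical analysis and sample size, state before the data are analysed that:

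- the primary analysis is a linear model with arm and surgeon, or the van Elteren test stratified by surgeon if a rank test is used;
- the repeated-measures models include surgeon as a factor;
- proportions are compared by Cochran-Mantel-Haenszel stratified by surgeon where counts allow.

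In Randomization and blinding, state the number of surgeon strata and whether allocation is blocked within them, so that a reader can tell which of the two cases above applies.

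The cost is a few sentences and one degree of freedom per additional surgeon stratum. No new data are needed, since surgeon must be known at randomisation. With two strata and no surgeon effect, power is unchanged at 85.1%. The planned 42 per group need not change.

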**Anesthesia and analgesia**

While in the operating room, all enrolled patients will be continuously monitored for standard measures including electrocardiogram, heart rate, non-invasive arterial blood pressure and oxygen saturation. Monitoring of Narcotrend Index (NI) is used for assessing patients’ depth of consciousness. Placement of a peripheral vein catheter is established for infusion. Radial artery catheterization is performed to monitor invasive arterial pressure and to measure blood gas.

After induction of total intravenous anesthesia with propofol/sufentanil/cis-atracurium, positive pressure ventilation will be performed in the patients of control group by ETI and in the patients of TAP+LMA group by LMA. Auscultation of respiratory tone, observation of respiratory parameters and examination with a flexible fiberoptic bronchoscopy is used to determine whether the laryngeal mask is in correct position. If necessary, gastric tubes will be placed with the help of a laryngoscope in the patients of control group or through the esophageal drainage tube of the LMA in the patients of the TAP+LMA group. Then, the procedures of ultrasound-guided subcostal TAP block will be implemented as described above.

Maintenance of anesthesia is achieved by administration of sevoflurane, remifentanil and cis-atracurium. Dosages of anesthetic drugs is adjusted to maintain arterial blood pressure and heart rate fluctuating in the range of -20% to +20% of the base value and NI fluctuating in the range of 37 to 56. If necessary, cardiovascular active drugs (i.e. norepinephrine, atropine, esmolol, nicardipine) will be used to maintain stable hemodynamics. Controlled-low Central Venous Pressure (CVP) technology is adopted to maintain CVP between 0 and 5 cmH_2_O during hepatectomy. This is done by restriction of fluid, control of anesthesia depth and stress response, adjustment of patients’ position, and application of vasoactive drugs (nitroglycerin and dobutamine). The CVP value will be restored to normal after completing the hepatectomy. Allogeneic blood transfusion will be administered if hemoglobin was less than 70 g/L. Body temperature is continuously monitored and maintained within 36～37℃ by multiple approaches including warmed infusion, application of electric blanket and preheated peritoneal irrigation.

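### The protocol declares every assessor blinded, but those working in the operating room cannot be, those recording airway removal may not be, and for the discharge surgeons no safeguard is stated

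*Protocol*

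**What the plan says.** Under Randomization and blinding, the Protocol appoints two anesthesiologists who "will perform all the intraoperative assessments", two others for all postoperative assessments, two surgeons who "will assess if the patients achieve the standard of hospital discharge", and two analysts. It then states: "All these investigators are blinded to the group allocation". The one person said to know the allocation is the operator for block and airway: "All procedures of TAP blockades and intubation or insertion of LMAs will be performed by the same anesthesiologist".

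Under Anesthesia and analgesia, the arms are ventilated differently: "positive pressure ventilation will be performed in the patients of control group by ETI and in the patients of TAP+LMA group by LMA". The route of any gastric tube differs too: "gastric tubes will be placed with the help of a laryngoscope in the patients of control group or through the esophageal drainage tube".

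Interventions describes two dummies: a saline TAP block in the control arm and saline wound infiltration in the TAP+LMA arm. No dummy, screen or cover is described for the airway.

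Study end-points includes "time to removing ETT or LMA" among the postoperative variables. It makes time to readiness for discharge the primary endpoint, judged against a list of criteria.

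**The concern.** A blanket statement of blinding covers people whose task puts the arm in front of them. Two consequences follow.

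First, data collected in the operating room would be reported as blinded when they are not. These include anesthetic and vasoactive doses and blood loss. Blood loss is more than descriptive, because under Patients a loss above 1000 ml removes a randomized patient from the analysis.

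Second, the raters of pain and QoR-40 may learn the arm before they rate, if they are the ones who record removal of the device. A pain score below 4 is also one of the discharge criteria, so knowledge at that step could reach the primary endpoint.

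A separate and weaker issue concerns the discharge surgeons. Several of their criteria need judgement (wound healing, organ function, independence), and their blinding is asserted without a stated means of protecting it.

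**Working it through.** **Blinding, group by group.** The blinding statement contains no figure, so this check sets the provisions side by side.

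| Group declared blinded | What the Protocol has them do | What reveals or hides the arm | Result |
|---|---|---|---|
| Intraoperative anesthesiologists | All assessments during surgery | Tube or LMA in place throughout; gastric tube route differs; only block and infiltration are masked | Claim not credible |
| Postoperative anesthesiologists | All postoperative assessments | Device removal time is listed as a postoperative variable, so by the text it is theirs to record; pain and QoR-40 (days 1 and 3, and discharge) follow | Claim fails if they record removal; feasible otherwise |
| Discharge surgeons | Judge readiness | Device long since out (planning means 7.5 and 9 days); no rule separates them from the operating team | Feasible, but unprotected |
| Analysts | Statistical analysis | No exposure to the patient described | Feasible |

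That staff in the operating room see the airway is an inference from the setting. It is a safe one for anesthesiologists assessing a ventilated patient, and less safe for an operating surgeon, who may be behind a drape.

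**The plan's own figure.** Inputs from Statistical analysis and sample size: means 9 and 7.5 days, SDs 2.5 and 2.0, two-sided α 0.05, power 85%.

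- Difference = 9 − 7.5 = 1.5 days.
- Pooled SD = √((2.5² + 2.0²)/2) = √5.125 = 2.264 days.
- The exact two-sample t-test at 42 per group has 85.1% power, so the stated 42 reproduces.

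**What a shift in the discharge judgement would do (illustration only).** The documents give no size for any assessment bias, so the shift is an assumption shown over a range. Take no true difference, 42 per group and a common SD of 2.264.

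- SE = 2.264 × √(2/42) = 0.494 day.
- Noncentrality = shift / SE. Type I error = P(|T| > t₀.₉₇₅,₈₂), with T noncentral t on 82 degrees of freedom.

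| Assumed mean between-arm shift (days) | Shift / 1.5 | Shift / SE | Two-sided type I error |
|---|---|---|---|
| 0 | 0 | 0 | 5% |
| 0.25 | 1/6 | 0.51 | 8% |
| 0.5 | 1/3 | 1.01 | 17% |
| 0.75 | 1/2 | 1.52 | 32% |
| 1.0 | 2/3 | 2.02 | 52% |

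The result is set entirely by the assumed shift. The table shows how sensitive the test would be if the assessors knew the arm. It is not evidence that they do.

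**The case against.** The best defence concerns the primary endpoint. The Protocol designates two surgeons for the discharge judgement and requires them to be blinded, so what is missing is the mechanism and not the requirement. The injections are matched by saline dummies, and readiness is judged days after the airway device is gone. Some criteria, such as white cell count and absence of fever, leave little room for opinion, which limits how far an assessor could move the date if all must be met. All of this stands.

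A reader might go further and infer that the discharge surgeons are the operating surgeons, that they saw the airway, and that the primary test is therefore biased. Stratification by surgeon with two random digit tables invites that reading. The documents do not support it. They do not say what the two tables are for or how many surgeons operate. Personal names are removed from the public text, so overlap can be neither shown nor excluded. No section says that an operating surgeon can see the airway.

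A second defence is that intraoperative variables are mostly laboratory values, durations, volumes and doses, and that none is the primary endpoint or a named secondary endpoint. This limits the consequence but does not make the statement true, and blood loss feeds an exclusion rule. Pain scores and QoR-40 are the patient's own answers, which also limits a rater's influence without removing it.

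**Conclusion.** The point holds in three grades.

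- **Intraoperative assessors:** the Protocol claims a blinding that its design does not provide. This rests only on the visible device and the absence of any described concealment.
- **Postoperative assessors:** on the literal text they learn the arm at device removal, before rating pain and QoR-40. This assumes that the words giving them all postoperative assessments include the removal time, which the Protocol lists as postoperative.
- **Discharge surgeons:** blinding is achievable but only asserted. That the primary endpoint is biased is not established, and the 8% to 52% range depends on assumed shifts for which the documents give no basis.

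The defect does not extend to the analysts, or to ward raters who did not witness removal. It should be corrected, because the trial describes itself as evaluator-blinded and the correction is cheap.

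**What to change.** 1. Limit the blinding statement to ward assessments, discharge-readiness assessments and the analysts. Report intraoperative and device-removal data as unblinded.
2. Have the already unblinded anesthesiologist, or the intraoperative staff, record the time of device removal, so that those who later score pain and QoR-40 do not witness it.
3. State that the surgeon judging a patient's discharge readiness took no part in that patient's operation and has no access to the anesthesia record.

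The cost is a less favourable description of blinding and minor scheduling effort. Items 1 and 2 need wording and a reassigned task only. Item 3 needs a further assessor only if both designated surgeons took part in the same operation.
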